**12.3 Withdrawal from the Study (Early Termination)**

Volunteers may be withdrawn from the study permanently for the following reasons:

1. Volunteers may withdraw from the study at any time if they wish, for any reason.
2. The principal investigator or designee has reason to believe that the volunteer is not complying with the protocol.
3. If the sponsor decides to terminate or suspend the study.

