##### *Intracellular drug concentrations:*

- The mean intracellular drug concentration for each group assigned to FTC/TDF

*Adherence:*

- The proportion of volunteers, who by MEMS data, took at least 80% of expected doses of the investigational product
- The proportion of volunteers assigned to FTC/TDF who have detectable drug plasma levels within 48 hours of reported use
- The relationship between intracellular drug levels and adherence in volunteers assigned to FTC/TDF

*Behavioural:*

- Reported number of steady and casual sex partners
- Frequency of unprotected vaginal intercourse
- Substance use prior to or during sex

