#### **6.5 Week 16 /Early Termination Visit for HIV-uninfected volunteers**

Assessments and procedures will be performed according to the Schedule of Procedures (Appendix A1).

Research centre personnel will:

- Review interim medical history and use of concomitant medications
- Perform a general physical examination including weight, vital signs (pulse, respiratory rate, blood pressure and temperature), examination of skin, respiratory, cardiovascular and abdominal systems, and external genital exam.
- Collect blood and specimens for tests as specified in the Schedule of Procedures (Appendix A1).
- Perform a pregnancy test for all female volunteers.
- Conduct HIV pre-test counselling or provide post-test counselling if the results of a prior HIV test are being provided to the volunteer.
- Collect data on Adverse Events and Serious Adverse Events
- Upload MEMS data
- Collect self-report information on adherence, sexual risk behaviour, investigational product acceptability and medication sharing (i.e., follow back interview)
- Collect unused pills and MEMS TrackCap

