### **7.6 Adherence Counselling**

Adherence counselling will be performed at time points according to the Schedule of Procedures (Appendix A1). At each follow-up visit, research centre personnel will assess volunteer adherence through a structured interview (follow back timeline) and pill count.

The structured interview will focus on self-reported adherence to the study medication, self-reported sexual activity, drug sharing, and challenges to adherence since the last visit (e.g., travel, illness, etc.). Research centre personnel will provide individualized adherence counselling at each follow-up visit, using the answers to the structured interview and pill count to guide the counselling messages.

Adherence counselling should include the following elements:

- Basic education about study medications such as mechanism of action, dose and dosing schedule, potential side effects, and storage
- Discussion of the volunteer's beliefs and attitudes about taking the investigational product
- Encouragement to talk to study personnel about medication questions or concerns
- Identifying and overcoming barriers to adherence, such as scheduling and organizational skills, reminder devices, social support, and disclosure.
- Discussion about reasons not to engage in pill-sharing and how to handle requests from friends and family to borrow doses

Complete information on procedures for adherence counselling is described in the Study Operations Manual.

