#### **14.2.5 Intracellular drug concentration**

Assuming Week 16 intracellular drug concentration has a log-normal distribution with a between subject standard deviation of 1.0 on the natural logarithm scale, this study should have about 79% power to rule-out a two-fold or greater relative decrease in the geometric mean concentration due to intermittent versus daily FTC/TDF. If the between subject standard deviation is 0.5, then there will be about 80% power to rule-out a 1.5-fold or greater decrease in the geometric mean concentration.

Pharmacokinetic (PK) modelling using plasma and intracellular drug concentrations will be performed to estimate individual PK parameters based on 2 drug levels following an observed dose, body weight, and creatinine clearance, and informed by population-PK parameter estimates. The MEMS data will be combined with the individual PK

estimates to simulate concentration-time relationships for the study. The PK-MEMS simulated concentrations will be compared to observed concentrations to evaluate plausibility of the reported dosing behaviour in comparison to that which is observed. Individual estimates of mean trough concentrations (plasma and intracellular) will be estimated. Comparisons between intermittent and daily regimen will be compared using actual and simulation-based values.

Intracellular drug levels will be correlated with pill count and self report data for those volunteers reporting drug use in the past 48 hours. Levels of drug in hair samples will be evaluated for exploratory purposes only.

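### Section 12.3 lets the investigator withdraw volunteers for non-compliance without exempting missed doses or phone reports, so poor adherers can leave the later adherence and Week 16 drug-level data

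*Protocol*

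**What the plan says.** Section 12.3 opens with "Volunteers may be withdrawn from the study permanently for the following reasons", and its second item is that "The principal investigator or designee has reason to believe that the volunteer is not complying with the protocol". It sets no threshold and makes no exception for non-adherence to product or to daily phone reporting.

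Three of the primary endpoints in Section 5.1.1 depend on that same behaviour:
- "The proportion of volunteers, who by MEMS data, took at least 80% of expected doses of the investigational product"
- "The mean intracellular drug concentration for each group assigned to FTC/TDF"
- "The relationship between intracellular drug levels and adherence in volunteers assigned to FTC/TDF"

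Staff learn about adherence while the trial runs. Section 7.6 states that at each follow-up visit "research centre personnel will assess volunteer adherence through a structured interview (follow back timeline) and pill count". Appendix A1 schedules the interview at Weeks 1, 2, 4, 8, 12 and 16, with pill counts and MEMS uploads from Week 4. The regimen is not blinded (Sections 5.2 and 7.12).

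At the Week 16 or early-termination visit, Section 6.5 has staff "Collect unused pills and MEMS TrackCap". Section 12.4 asks for the termination procedures only where they can be done. Section 14.2.5 bases its power statement on Week 16: "Assuming Week 16 intracellular drug concentration has a log-normal distribution". Section 14.2.4 analyses adherence month by month and tests for decline. Section 14.2 uses all randomized volunteers who were HIV-1 negative at randomization, and Section 12.2 does not replace those who are discontinued.

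**The concern.** Not taking the tablets, or not answering the daily call, can be read as not complying with the protocol. In this pilot it is also the outcome. A rule that lets staff end participation on this ground makes loss to follow-up depend on the primary outcome. The volunteers most likely to go are those with the lowest adherence and, presumably, the lowest drug levels.

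After withdrawal there is no cap, no later month of adherence and no true Week 16 sample. No analysis rule can recover data that were not collected. With 24 volunteers per active group, a few such withdrawals would be visible in the estimates used to design the next trial.

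**Working it through.** **The plan's own figures.** An exact two-sided 0.05 binomial test of 75%, with 0.025 in each tail, rejects at ≥23 or ≤13 of 24, and at ≥33 or ≤21 of 36. Power at true rates of 90% and 95% is 29.2% and 66.1% (n=24) and 50.9% and 89.6% (n=36). Section 14.2.4 states 29%, 66%, 51% and 90%, so its figures reproduce. For Section 14.2.5 (24 v 24, normal approximation), SD 1.0 and a 2-fold margin give 77.5% at one-sided 0.05 (stated 79%). SD 0.5 and a 1.5-fold margin give 80.2% at two-sided 0.05 (stated 80%). The stated powers are not in dispute here.

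**Week 16 geometric mean.** SD 1.0 and 0.5 come from Section 14.2.5. The number withdrawn (k) and the correlation ρ between adherence and log level are not in the document and are assumed. If the k lowest adherers of 24 are missing, the geometric mean is multiplied by about exp(ρ × SD × m_k), where m_k is the mean of the remaining standard normal order statistics. By simulation m_2 = 0.158 and m_4 = 0.287.

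| SD | k | ρ=0.3 | ρ=0.5 | ρ=0.8 | ρ=1.0 |
|---|---|---|---|---|---|
| 1.0 | 2 | +5% | +8% | +13% | +17% |
| 1.0 | 4 | +9% | +15% | +26% | +33% |
| 0.5 | 4 | +4% | +7% | +12% | +15% |

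**Comparison of regimens.** Suppose the true decrease sits exactly at the margin (2-fold, SD 1.0, one-sided 0.05) and only the intermittent group loses its lowest adherers. The chance of wrongly ruling out that decrease rises from 5% to 9–15% (k=2) or 13–28% (k=4) for ρ of 0.5 to 1.0. If only the daily group loses them, the daily mean rises and the comparison becomes conservative.

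**Later monthly adherence (assumed example).** Take 20 volunteers at 95% and 4 at 30%, and withdraw 3 of the 4.
- Mean: (20×95 + 4×30)/24 = 84.2% becomes (20×95 + 30)/21 = 91.9%.
- Proportion above 90%, which Section 14.2.4 models over time: 20/24 = 83.3% becomes 20/21 = 95.2%.
- Median: 95% in both cases, so not every monthly summary moves.

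**Overall 80% endpoint.** If the withdrawn volunteers in that example are scored on their data up to withdrawal, they remain failures and the result stays 20/24 = 83.3%. If non-adherers are instead dropped, 27/36 = 75.0% becomes 27/34 = 79.4% (k=2) or 27/32 = 84.4% (k=4). The chance of wrongly concluding adherence above 75% then rises from 1.1% to 8.4% or 16.8%. For n=24, 18/24 = 75.0% becomes 18/22 = 81.8% or 18/20 = 90.0%, and the error rises from 0.9% to 11.5% or 42.2%.

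**The case against.** The item is permissive, and the rest of the protocol leans towards keeping poor adherers. Section 7.6 answers poor adherence with counselling. Section 6.6.2 interviews those who report under 80%. Section 12.1 does not list non-adherence as a reason to stop product. The persistence definition in Section 14.2.4 needs non-users to stay under observation. All of this stands, and it suggests that withdrawal for missed doses is not intended. None of it forbids such withdrawal or requires follow-up after it.

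A reader might infer more than the documents support:
- **That all low drug levels are lost.** They are not. The Week 16/early-termination column of Appendix A1 includes MEMS upload, drug levels, PBMCs and hair, and levels are also drawn at Weeks 4, 8 and 12. What is lost is the later months and a true Week 16 value.
- **That the 80% endpoint must be inflated.** The analysis set in Section 14.2 can keep withdrawn volunteers as failures. How they are scored may be settled in a statistical analysis plan that is not at hand.
- **That the rule falls more heavily on the daily groups.** This is conjecture. Missed Monday and Friday doses are also visible, and phone reporting applies to every group.
- **That withdrawn volunteers are censored as persistent.** Section 14.2.4 names censoring only for intolerance, toxicity and pregnancy.
- **That the inflation is about one third.** That is the top of the assumed range. In the example above, levels proportional to adherence give exp(ln(95/30) × (4/24 − 1/21)) = 1.15, or 15%.

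**Conclusion.** The point holds as a gap in the withdrawal rule. Section 12.3 permits loss of follow-up that depends on the primary outcome, and nothing elsewhere in the protocol closes it. The exposed quantities are later monthly adherence, the test for decline and the Week 16 geometric means.

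The size is conditional. With n=24, 2 to 4 lowest adherers missing, SD 1.0 and correlation 0.3 to 1.0, the Week 16 geometric mean is inflated by about 5% to 33%. With SD 0.5 and four missing, it is about 4% to 15%. The number withdrawn and the correlation are assumptions, and whether the regimen comparison would be favoured or penalised cannot be told. The overall 80% endpoint is at risk only if withdrawn volunteers are dropped or change class on their shortened period. This is a cheap improvement, not a fault that invalidates the design.

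**What to change.** Add one sentence to Section 12.3, item 2: non-adherence to investigational product, or to IVR/SMS reporting, is not by itself a ground for investigator withdrawal from the study; such volunteers keep the MEMS cap and continue the scheduled visits and samples, including Week 16.

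This concerns follow-up and data collection only. Section 12.1 on stopping product stays unchanged, as do the follow-up rules in Sections 11.2.3 and 12.2, which keep volunteers who become HIV-infected, and those discontinued for adverse events, out of the Week 24 visit. A volunteer's own right to withdraw is also untouched.

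The cost is one sentence in an amendment, plus continued follow-up of some poorly compliant volunteers at visits already scheduled.

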**12.4. Follow-up Withdrawal from the Study (Early Termination)**

If the volunteer withdraws from the study, all termination visit procedures will be performed according to the Schedule of Procedures (Appendix A1) when

possible. Every effort will be made to determine and document the reason for withdrawal from the study.

## **13.0 DATA HANDLING**

### **13.1 Data Collection and Record Keeping at the Study Research centre**

Data Collection: All study data will be collected by the clinical study staff using designated source documents and entered onto the appropriate case report forms (CRFs). CRFs will be provided by IAVI and should be handled in accordance with the instructions from IAVI. All study data must be verifiable to the source documentation. A file will be held for each volunteer at the clinic(s) containing all the source documents. Source documentation will be available for review to ensure that the collected data are consistent with the CRFs.

All CRFs and laboratory reports will be reviewed by the clinical team, who will ensure that they are accurate and complete.

Source documents and other supporting documents will be kept in a secure location and remain separate from volunteer identification information (name, address, etc.) to ensure confidentiality.

Standard GCP practices will be followed to ensure accurate, reliable and consistent data collection.

*Source documents include but are not limited to:*

- Signed Informed Consent Documents
- Dates of visits
- Documentation of any existing conditions or past conditions relevant to eligibility
- Reported laboratory results
- All adverse events
- Concomitant medications
- Questionnaires

### **13.2 Data Entry at the Study Research Centre**

The data collected at the research centre will be entered onto the CRFs by the research centre personnel. To provide for real time assessment of safety, data should be entered as soon as reasonably feasible (e.g., within one week) of a visit.

### **13.3 Data Analysis**

The data analysis plan will be developed and agreed upon by the sponsor, the principal investigators and Study Chair prior to unblinding of the study. The statistician at the Data Coordinating Centre, in collaboration with the Principal Investigators and the Sponsor, will create tables according to this data analysis plan.

The DCC will conduct the data analysis and will provide interim and final study reports for the sponsor, principal investigator, the SRB and the regulatory authorities as appropriate. Senior statisticians at the collaborating research centre may participate in data analysis.

## **14.0 STATISTICAL CONSIDERATIONS**

### **14.1 Sample Size**

Approximately 72 volunteers (24 daily FTC/TDF, 24 intermittent FTC/TDF, and 24 combined placebo recipients) who meet all eligibility criteria will be enrolled in the study.

### **14.2 Statistical Power and Analysis**

Prior to the analysis of safety, adherence, risk behaviour, and HIV-specific immune response data, integrity of study conduct and study group comparability will be examined to assure the validity of study results. All analyses will be based on the modified intention-to-treat cohort defined as all randomized individuals who are HIV-1 negative at the time of randomization. Volunteers will be analyzed according to the group to which they were randomized.

#### **14.2.1 Safety and tolerability**

Adverse events will be classified according to the MedDRA body system and preferred terms. The number and percentage of subjects experiencing a given AE will be tabulated by treatment group, grade (severity/ relationship), and time since randomization.

Safety and tolerability will be assessed by examining the overall rates of adverse events and serious adverse events that are possibly, probably, or definitely associated with FTC/TDF. With 24 volunteers assigned to daily or intermittent FTC/TDF, observing no drug-related serious toxicity would result in an exact, two-sided, 95% confidence interval of (0.0000, 0.1425). If one drug-related SAE is observed, the exact, two-sided, 95% confidence interval would be (0.0011, 0.2112).

This study will have limited power to rule out all but very large relative increases in the risk of an adverse event due to FTC/TDF. For example, if 5% of the volunteers in the combined control group are expected to experience a given AE, this study has only 55% power to rule out a 10-fold increase (i.e., 5% vs. 50%) if there is no real increase. It has 63% power to rule-out a 15-fold increase (5% vs. 75%). For known FTC/TDF toxicities in HIV-infected persons, the observed AE rate among FTC/TDF recipients will be compared to historical data.

All clinical and routine laboratory data will be included in the safety analysis. Rate of study discontinuation and reasons for discontinuation will be determined by treatment group.

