### 3.3 Clinical data

#### 3.3.1 Clinical data in HIV-infected persons

TDF was approved by the U.S. Food and Drug Administration in 2001 as a treatment for HIV infection. FTC/TDF, the TDF plus FTC combination pill, was approved for use as an HIV treatment in 2004. More than 200,000 HIV-infected people around the world have now used these drugs. In HIV-infected persons, TDF and FTC have both been studied as components of multi-drug regimens and were found to be safe and effective in treating HIV infection by lowering HIV viral load [41,43]. They have relatively low levels of side effects and slow development of associated drug resistance, compared with other antiretroviral drugs. They are also among the most convenient antiretrovirals, dosed orally once a day with or without food. Because TDF and FTC were developed for treatment of HIV infection, the large majority of clinical safety data is from HIV-infected patients, who may have symptoms due to their HIV-infection or associated conditions, and who use the drug(s) in combination with other antiretrovirals and HIV-related medications with their own side effect profiles. Therefore, safety data from HIV-infected patients may not represent the safety profile in HIV-uninfected persons.

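### For known FTC/TDF toxicities, the only rate comparison Section 14.2.1 commits to is against historical data; the concurrent placebo contrast should be the main reading

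*Protocol*

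**What the plan says.** Section 14.2.1 (Safety and tolerability) contains four relevant elements.

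- Tabulation: "The number and percentage of subjects experiencing a given AE will be tabulated by treatment group, grade (severity/ relationship), and time since randomization". Placebo recipients are therefore included in the tables.
- One-sample exact confidence intervals for drug-related serious events in a group of 24.
- A statement of limited power against the combined control group, for example "this study has only 55% power to rule out a 10-fold increase (i.e., 5% vs. 50%) if there is no real increase".
- The sentence at issue: "For known FTC/TDF toxicities in HIV-infected persons, the observed AE rate among FTC/TDF recipients will be compared to historical data".

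No source, reference rate, test or significance level accompanies that sentence. Section 14.1 gives the groups as "24 daily FTC/TDF, 24 intermittent FTC/TDF, and 24 combined placebo recipients", and Sections 5.2 and 7.12 describe a randomized design that is blinded as to active or placebo. Section 3.3.1, on the experience in HIV-infected patients, warns that "safety data from HIV-infected patients may not represent the safety profile in HIV-uninfected persons".

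**The concern.** The first primary objective is the safety of daily and intermittent FTC/TDF, and the volunteers who take it are HIV-uninfected. The named comparison for known toxicities answers a different question: whether their rate resembles one seen elsewhere. The difference between the two rates mixes four things:

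- the effect of the drug;
- the local background rate of the same event;
- time at risk: drug stops at week 16 here (Section 6.7), while the renal trials cited in Section 3.3.1 ran 44 to 144 weeks and the renal case reports began at 5 to 16 months;
- population and regimen: HIV disease, other antiretrovirals and once-daily dosing there, and intermittent dosing for half of the active recipients here.

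The bias can go either way. A higher local background makes a harmless regimen look toxic. Shorter exposure makes a harmful one look unremarkable. The concurrent placebo group shares background, follow-up and ascertainment, so it removes these differences by design. For HIV-specific immune responses, Section 14.2.8 names a Fisher test against placebo. For known toxicities, Section 14.2.1 names no placebo contrast.

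**Working it through.** **1. The plan's own figures.** For 0 events in 24, the exact upper limit is 1 − 0.025^(1/24) = 0.1425. For 1 in 24, the Clopper-Pearson limits are 0.0011 and 0.2112. Both match. The power figures of 55% and 63% for ruling out 10-fold and 15-fold increases come without a stated method. With 48 against 24, 5% in both groups, a one-sided 5% log risk-ratio limit and both counts non-zero, exact enumeration gives 56.7% and 63.6%, within 2 points of each. The section therefore has a placebo contrast in mind when it states power, but it does not name one as an analysis.

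**2. Inputs for the illustration.** From the protocol: 24 volunteers per active arm, 48 combined, and 24 on combined placebo; laboratory abnormality rates of 2–12% in HIV-infected patients on TDF (Section 3.3.1). Assumed, because the documents do not give them: the historical rate applied to one toxicity, the local background, and the test.

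**3. No drug effect, historical rate 5%.** An exact two-sided 0.05 binomial test signals an excess at 6 or more events in 48 (upper tail 0.032 at 5%), or 4 or more in 24 (0.030). A 0.025 upper-tail test needs 7 or 5 events. The chance of a signal is P(X ≥ r | n, true background):

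| True background | n = 48, two-sided | n = 48, 0.025 upper tail | n = 24, two-sided | n = 24, 0.025 upper tail |
|---|---|---|---|---|
| 5% | 3.2% | 0.9% | 3.0% | 0.6% |
| 10% | 34.7% | 20.0% | 21.4% | 8.5% |
| 15% | 74.6% | 59.4% | 49.5% | 28.7% |

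With equal rates of 5–20% in both groups, Fisher's two-sided test of 48 against 24 placebo rejects 1.9–3.3% of the time counting both directions, and at most 1.5% in the direction of harm.

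**4. Exposure time.** Suppose a 12% historical rate accrued at a constant hazard over 48 weeks (assumed). The same hazard over 16 weeks gives 1 − 0.88^(16/48) = 4.2%. Three times that hazard gives 1 − 0.88 = 12.0%, exactly the historical figure.

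**5. Sensitivity to harm.** Take a placebo risk of 4%, an active risk of 12% and a historical rate of 12%. The test against the historical rate signals at 7 or more in 24 (1.9%) or 11 or more in 48 (2.5%). Fisher's test against 24 placebo recipients detects the tripling 6.5% of the time with 24 active and 8.4% with 48. With the 4.2% and 12.0% of step 4, the Fisher figures are 6.2% and 8.0%.

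**The case against.** A reader might infer three stronger things, and the documents support none of them.

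- That the placebo group is set aside. It is not: every event is tabulated by treatment group, power is stated against the combined control, and all clinical and routine laboratory data enter the safety analysis. Coming straight after the admission of limited power, the historical sentence reads as an addition.
- That a specified test has a faulty alarm rate. No test, null hypothesis or threshold is stated, so the percentages above describe one natural way of carrying out the comparison, under assumed rates. A stricter test lowers them, and a background equal to the historical rate removes the excess.
- That the historical comparator is why a tripled risk would be missed. Fisher's test against placebo also misses it more than 90% of the time. This is mainly a limit of sample size, which the protocol discloses.

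It is also fair to say that the phrase about HIV-infected persons grammatically describes the toxicities rather than the data source. Section 3.3.2 reports a placebo-controlled trial in 936 HIV-uninfected women that could serve as historical data. But that trial gave TDF alone, daily, for 12 months to women in West and Central Africa, so it does not replace concurrent controls for FTC/TDF in two regimens.

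What remains is narrower. The sentence does commit to a historical comparison, it is the only comparison of rates named for these toxicities, and the protocol itself doubts the most likely source.

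**Conclusion.** The point holds as a poor choice of reference, not as an omission of placebo data. For known toxicities, the one rate comparison to which the protocol commits cannot distinguish a drug effect from differences in background, exposure or population. Its size cannot be fixed from the documents. With a 5% historical rate and a true background between 5% and 15%, the chance of a spurious excess in 48 active volunteers runs from about 3% to 75% with a two-sided exact test, or 1% to 59% with a 0.025 upper-tail test; against placebo it stays near 3% or below. Detection of a tripled risk is low either way: about 2% against the historical rate and 6–8% against placebo. The gain from the change is therefore freedom from bias and an honest display of uncertainty, with little gain in sensitivity. It is worth making because the trial already collects the data it needs.

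**What to change.** Replace the historical-comparison sentence in Section 14.2.1 with wording such as: for known FTC/TDF toxicities, the rate in each FTC/TDF arm and in both arms combined will be compared with the combined placebo group by the risk difference and its 95% confidence interval (exact or Newcombe), and this is the main reading; historical rates, with source, population and exposure time named, will be shown as descriptive context and no conclusion will rest on them.

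The cost is one sentence and no new data. The interval becomes wider because the comparator is 24 volunteers and not a fixed rate. At 10% in both groups (assumed) and by the normal approximation, the 95% half-width for 48 against 24 is 1.96 × √(0.09/48 + 0.09/24) = 1.96 × 0.075 = 14.7 percentage points. Against a fixed rate it is 1.96 × √(0.09/48) = 8.5 points. The extra width is uncertainty about the background rate, which a fixed historical figure leaves out.
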